### Sample Size Estimation

Sample size was calculated considering as primary outcome measure the proportion of patients, in the transplantation group with respect to controls, displaying a “positive response” intended as an increase in the proportion of Treg by at least 20%. The null hypothesis states that FMT does not ameliorate significantly the proportion of positive responses in treated patients after the second FMT round, compared to their baseline and to control group. The alternative hypothesis is that FMT gives a proportion of positive responses in at least 50% of treated patients compared to a maximum 5% of positive responses in patients of the control group. The study was designed to refuse the null hypothesis with an alpha error of 0.05 and a power of 0.80 according to previously published statistical methods (26) and to known levels of Tregs in ALS patients, that typically display a slight reduction of Treg % (mean ± standard deviation: 2.1 ± 0.7) with respect to healthy controls with fast progressors patients having on average 31% fewer Treg (8, 27).

For this purpose, a population of 39 patients randomized in two treatment arms would suffice; taking into account an average drop out of 10%, a recruitment of 42 patients will be needed.

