### Outcome Measures

Primary outcome measure is the modification from baseline to month 6 in Treg number in transplanted ALS patients compared to the control arm (26).

Secondary outcome measures include the following:

✓ Biological outcome measures:–Change from baseline to month 3, 6, 9, 12 of the T cell distribution especially the ratio Treg/Th1 or Treg/Th17 comparing FMT arm and control arm (both blood—at each time point, and small intestine—only at 6 and 12).–Changes from baseline to month 3, 6, 9, 12 in inflammatory status (cytokine profile) comparing FMT and control arm (in blood and feces at each time point, and in CSF at month 6).–Changes from baseline to month 3, 6, 9, 12 between FMT arm and control arm in the following biomarkers: creatinine, albumin, CK, vitamin D, plasma/CSF neurofilament heavy/light chain protein.–Biological modifications from baseline to month 6 and 12 in the composition of saliva, gut and fecal microbiota (including SCFA) comparing FMT and control arm.✓ Safety: will be assessed in FMT and control arm considering the occurrence of AEs and modifications in physical examination, vital signs, body weight, and laboratory tests (biochemistry, hematology) during and following the treatment.✓ Clinical outcome measures:The following clinical variables will be compared between FMT and control arm:– Change from baseline to each time point (month 1, 3, 6, 9, 12) of ALSFRS-R.– Survival from onset and randomization to death or tracheotomy.– Change of Forced Vital Capacity (FVC) from baseline to each time point (month 1, 3, 6, 9, 12).– Frequency of procedures (PEG, NIV, IV) from baseline to month 3, 6, 9, 12.✓ Quality of life: will be assessed as the change in absolute and relative values of the Amyotrophic Lateral Sclerosis Specific Assessment Questionnaire (ALSAQ40) from baseline to month 6 and 12 in FMT and control arm.

The Table 3 shows the study flow chart.

**Table 3 T3:** Study flow chart.

	**Pre-treatment**		**Treatment**					**Follow up**			**Study end**
**Examinations**	**Screening**	**Baseline (W0)**	**FMT 1 (Rome)**	**M1**	**M3**	**M6**	**FMT 2 (Rome)**	**M7**	**M9**	**M12 (Rome)**	**M12**
**Time window**		** <3 weeks from screening**	** <4 weeks from screening**	**±3 days**	**±3 days**	**±3 days**	**±7 days**	**±7 days**	**±7 days**	**±7 days**	**≥7 days <4 weeks from M12**
Informed consent	x										
Medical history	x										
Inclusion exclusion criteria	x										

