### Data Analysis

Data will be collected by investigators through electronic CRF, which will be conveyed to the trial database. At trial completion, data from the locked database will be extracted for analysis by an expert statistician.

Separate analyses will be performed in:

All randomized subjects receiving at least 1 FMT (Intention-to-treat population).All randomized subjects excluding protocol deviations (Per protocol population).

As far as biological activity is concerned, immune response to FMT will be analyzed as a difference in positive response to FMT between the control group and the FMT group, assessed by comparison of proportion of patients in the two groups showing a mean Tregs increase by at least 20%, between baseline and month 6 measurements.

Mean values of different T, B, NK cell subpopulations, neurodegeneration biomarkers, and cytokines will be assessed and mean differences in plasma concentrations between the two treatment arms will be calculated using *t*-test or Wilcoxon-Mann-Whitney test as previously reported (26). ANOVA will be used for assessing the mean change over time for the same variables as above, with treatment as between-subjects factor and time as within-subjects factor. Different models will be used, each with a different biomarker of activity as the dependent variable. Models will be adjusted for any unbalanced distribution of the main prognostic factors (e.g., age) between the two treatment arms, according to previously published statistical methods (26).

Analysis of microbiota will be performed with specific software.

Record of any AE and SAE will be kept for every subject receiving at least one round of FMT till the study completion, performing safety analysis accordingly.

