As for clinical outcome measures, we will compare ALSFRS-R total score and subscores (bulbar, respiratory, gross, and fine motor) changes from baseline to each time point in treatment arm vs. control arm. Frequency of procedures (PEG, NIV, IV) will be compared from baseline to each time point in treatment vs. control arm. The comparison of clinical endpoint among arms will be carried out by using the logistic regression model. Results will be presented as odds ratios (OR) and 95%C.I. FMT will be considered effective in relation to controls whether the OR of positive results will provide a *p* < 0.05. Change in FVC during the study will be analyzed using a mixed model for repeated measures (MMRM). Difference between treatment groups and two-sided 95% CI will be estimated .Log-rank tests via Kaplan-Meier method will be employed to compare differences in tracheostomy-free survival between the two treatment arms (from onset and from randomization), while Cox's proportional hazard model will be used for adjusting for any possible unbalanced prognostic factors. Statistical significance will be set at 0.05 level for a two-tailed test. Last observation will be considered for patients with missing data.

Given the short duration of the study, an interim analysis of efficacy data is not scheduled. Nevertheless, to address safety concerns, a report including all relevant clinical data of patients will be sent by the Statistics Unit to an independent Data and Safety Monitoring Board for scheduled DSMB meetings (also through Skype) when 14 patients would have completed the second treatment and then every 6 months.

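### Cell subsets, biomarkers and cytokines are to be compared by mean differences and mean change with no log scale and no baseline covariate; if the markers are right-skewed, log-scale analysis adjusted for baseline would gain power

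*Protocol article*

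**What the plan says.** In the protocol article, Data Analysis gives two methods for T, B and NK subsets, neurodegeneration biomarkers and cytokines.

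- **Between arms:** "mean differences in plasma concentrations between the two treatment arms will be calculated using" a t-test or, as an alternative, a Wilcoxon-Mann-Whitney test. The tests are referred to a published source. No rule says when each applies.
- **Over time:** "ANOVA will be used for assessing the mean change over time for the same variables as above", with treatment between subjects and time within subjects. Each biomarker in turn is the dependent variable. Adjustment is foreseen for prognostic factors found to be unbalanced, with age as the example. The marker's own baseline value is not named as a covariate.

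No transformation or geometric mean is mentioned. Outcome Measures defines the biological secondary outcomes as changes from baseline, among them the "T cell distribution especially the ratio Treg/Th1 or Treg/Th17 comparing FMT arm and control arm". Data Analysis does not name these ratios, so its T-cell methods reach them only by implication. The Treg response is handled separately, as a comparison of the proportions of patients with a rise of at least 20%.

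**The concern.** Concentrations and cell ratios cannot fall below zero, and treatment often changes them by a proportion rather than a fixed amount. Where such a marker is right-skewed, a few high values drive the arithmetic mean and inflate its variance, the more so with 14 controls. Raw differences then estimate a proportional effect inefficiently. The rank test helps in the two-arm comparison, but the longitudinal model has no counterpart.

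Ratios raise a second issue. A raw-scale result for the change in a ratio depends on which cell type is the denominator.

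At stake is sensitivity. The trial is meant to give the biological basis for planning a later efficacy study, so a real effect on a secondary marker could be missed.

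**Working it through.** **No stated figure to reproduce.** The article gives no power for these comparisons. Its sample size rests on responder proportions ("at least 50% of treated patients compared to a maximum 5% of positive responses") and does not bear on this point.

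**Inputs from the article**
- 28 FMT and 14 control patients (Study Design).
- Two-sided 0.05: "Statistical significance will be set at 0.05 level for a two-tailed test" (Data Analysis).
- Treg % 2.1 ± 0.7 (Sample Size Estimation), so CV = 0.7 / 2.1 = 33%. This is the only dispersion figure.

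**Assumptions**
- Log-normal data, and correlation 0.8 between baseline and follow-up on the log scale.
- A true 30% fall, or the mirror-image 43% rise (1 / 0.7 = 1.43).
- CVs of 60% and 100%.

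**Step 1. Simulated power, 28 vs 14**

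| Setting | Raw-change t-test | Raw-change Wilcoxon | Raw ANCOVA | Log ANCOVA |
|---|---|---|---|---|
| 30% fall, CV 60% | 68% | 73% | 83% | 90% |
| 30% fall, CV 100% | 30% | 38% | 41% | 55% |
| 43% rise, CV 100% | 34% | 48% | 35% | 57% |

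Separate runs of the same settings differ by up to about 3 points. With two time points, the ANOVA's time-by-treatment test equals the t-test on change, so the first column also stands for the ANOVA. Type I error is about 5% for all methods.

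**Step 2. Check of the log ANCOVA column by formula**

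Log SD: s = √ln(1 + CV²). Residual SD: s·√(1 − 0.8²) = 0.6·s. Standard error: 0.6·s·√(1/14 + 1/28) = 0.6·s·0.327. Effect: |ln 0.7| = 0.357. Critical t on 39 df: 2.02. Power ≈ Φ(effect/SE − 2.02).

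- CV 60%: s = 0.555, SE = 0.109, effect/SE = 3.27, power ≈ Φ(1.25) = 89%.
- CV 100%: s = 0.833, SE = 0.163, effect/SE = 2.18, power ≈ Φ(0.16) = 56%.
- CV 33%: s = 0.325, SE = 0.064, effect/SE = 5.6, power near 100%.

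These agree with the simulation.

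**Step 3. Separate baseline adjustment from scale (30% fall)**
- Raw-change t-test to raw ANCOVA (baseline adjustment): 83 − 68 = 15 points at CV 60%; 41 − 30 = 11 at CV 100%.
- Raw ANCOVA to log ANCOVA (scale): 90 − 83 = 7 points at CV 60%; 55 − 41 = 14 at CV 100%.

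**Step 4. CV 33%**

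With a 30% fall the methods nearly agree, but partly because power is near its ceiling. With the effect reset so that a log-change t-test has 80% power (correlation 0.5), the raw-change t-test has 80% for a rise and 71% for a fall. A raw t-test on levels has 76% and 80%. The loss is therefore between nothing and about 9 points.

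**Step 5. How a ratio is written**

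In the same calibrated simulation (correlations 0.5 and 0.7), raw-change t-tests on a ratio and on its inverse differ in significance at 0.05 in 16–17% of trials at CV 33% and about 40% at CV 100%. For Wilcoxon on raw change the figures are about 15–16% and 29–31%. On levels, Wilcoxon never differs. On the log scale the two versions are identical, since ln(1/x) = −ln x. In a separate run the two versions were never significant in contradictory directions (0 of 5,000 trials).

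**The case against.** - **The rank test is planned.** A reader might infer that only the t-test and ANOVA are used. The same sentence offers Wilcoxon-Mann-Whitney. On skewed levels it keeps nearly all the power (77–78% against 80% on the log scale), and on raw change it recovers part of the loss. What stands is that no rule selects it, the ANOVA has no such alternative, and the outcomes are defined as changes.
- **The skew is assumed.** The article gives no SD for any biomarker, cytokine or ratio. The log-normal model with a proportional effect also favours the log analysis by construction. This stands, so the larger losses are conditional.
- **Ratio orientation.** A reader might infer that the way a ratio is written could decide significance here, or that the same patients could yield opposite conclusions. The documents do not support this. Outcome Measures fixes Treg as the numerator, no inverse ratio is planned, and the discrepancy is significant versus not significant. Dependence on the way the ratio is written remains a weakness of the raw scale, but it leaves no choice open in this trial.
- **Detail left to an analysis plan.** Transformations are often specified there, and that document is not shown. This lowers the weight of the point. It does not remove it, because the article itself states mean differences and mean change as the targets.

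**Conclusion.** The point holds as an optional improvement to secondary outcomes. The stated method can be bettered for skewed markers by a log scale with the baseline value as covariate. For a 30% fall, log ANCOVA gains 90 − 68 = 22 points over the raw-change t-test at CV 60% and 55 − 30 = 25 at CV 100%. Scale alone accounts for about 7 and 14 of these; the rest comes from baseline adjustment. The sizes rest on assumed CVs, log-normality and correlation 0.8. At the one documented CV the difference is small.

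A reader might also infer a risk of false positives or a threat to the primary analysis. Neither follows: type I error is near 5% for every method, and the Treg responder comparison of proportions is not affected.

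**What to change.** For concentrations and cell ratios expected to be skewed, pre-specify before database lock:

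1. Analysis of log values with the baseline log value as covariate, in the repeated-measures model as well, whether or not baseline looks unbalanced.
2. Ratios of geometric means with 95% confidence intervals as the effect measure, with Treg/Th1 and Treg/Th17 named explicitly.
3. Wilcoxon-Mann-Whitney as a sensitivity analysis, in place of the open choice between two tests.
4. The raw scale for near-symmetric markers such as albumin.
5. A rule for values below the quantification limit, for example treating them as censored or using a rank-based sensitivity analysis.

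The cost is wording only, with no new data, since baseline is already measured. Effects will read as percent differences rather than absolute units, and the quantification-limit rule has to be written because logs cannot take zeros.

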**Figure 1 F1:**
[figure not shown]
Picture of the study design.

The study will include 42 ALS patients with 2:1 allocation in 2 groups of subjects (28 FMT vs. 14 controls). Patients will be screened in the 15 days before baseline; then they will be randomly allocated to either FMT or control group. Randomization will be 2:1 (FMT: controls) and will be performed on line (using a computer-generated list of random number that will be centrally generated in the Statistical Unit). Given the heterogeneous ALS progression, patients will be stratified by ΔFS (progression rate), calculated at randomization according to Kimura et al. (25). Riluzole will be maintained during the entire study duration unless adverse events or patients' decision to withdraw. Endoscopic treatment will be performed within 21 days from randomization. Randomization number will not be re-used in any case. Estimated enrolment time is 18 months.

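### The secondary biomarker and Cox models choose covariates by observed imbalance, a rule that normally leaves out ΔFS, the factor balanced by design

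*Protocol article*

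**What the plan says.** The Study Design section (text under Figure 1) gives the stratification factor and the reason for it: "Given the heterogeneous ALS progression, patients will be stratified by ΔFS (progression rate), calculated at randomization".

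The Data Analysis section describes the secondary biomarker comparisons in three steps:
- For group differences: "mean differences in plasma concentrations between the two treatment arms will be calculated using *t*-test or Wilcoxon-Mann-Whitney test".
- For change over time, an ANOVA "with treatment as between-subjects factor and time as within-subjects factor".
- For covariates: "Models will be adjusted for any unbalanced distribution of the main prognostic factors (e.g., age) between the two treatment arms".

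For tracheostomy-free survival the section names a log-rank test, not described as stratified, and then states: "Cox's proportional hazard model will be used for adjusting for any possible unbalanced prognostic factors".

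ΔFS is not mentioned in the Data Analysis section. The article does not define what counts as unbalanced, and age is the only prognostic factor it names. For the biomarker models it refers to previously published statistical methods. Baseline values enter through change from baseline or as a level of time, not as a covariate.

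The primary biological comparison is described separately, as a comparison of responder proportions, with no covariate: "assessed by comparison of proportion of patients in the two groups showing a mean Tregs increase by at least 20" percent.

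**The concern.** This is a stated selection rule, not a detail left open. As written it has two weaknesses.

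First, it conflicts with the design. ΔFS is used to stratify because progression is heterogeneous. Stratified randomisation balances ΔFS between the arms, so a rule that adjusts for what is unbalanced will normally pass over it. The standard error of an unadjusted comparison then still contains the between-stratum variance that stratification has removed from the treatment difference. Reported intervals are too wide and tests too cautious.

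Second, the remaining covariates are picked after allocation and baseline data are known, by a criterion the article does not define. A covariate strongly related to the outcome but balanced by chance is dropped, and the precision it would have brought is lost.

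What is at stake is the width of the intervals and the power for secondary biomarker and survival results. The trial has 42 patients and is meant to inform a later efficacy study.

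**Working it through.** **The plan's own figure.** The only calculated figure is the sample size: 39 evaluable and 42 enrolled, for 50% against 5% responders. A two-sided, continuity-corrected 1:1 calculation gives 38, close to 39. It belongs to the responder comparison and has no bearing on the covariate rule.

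**Inputs from the article.** 28 FMT and 14 controls; two-sided 0.05; stratification by ΔFS; Treg % 2.1 ± 0.7; fast progressors with on average 31% fewer Treg (Sample Size Estimation).

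**Assumed, because the article does not give them.** The number of ΔFS strata, the correlation of ΔFS or baseline with each outcome, and an effect of 0.9 SD for power.

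**Step 1: would the rule select ΔFS?** With permuted blocks of 3 within two or three ΔFS strata (assumed), an imbalance check at p < 0.05 flagged ΔFS in 0 of 4,000 simulated trials.

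**Step 2: effect of leaving out a balanced ΔFS in a linear model.** If the strata explain a share R² of outcome variance, the ratio of reported to true standard error is about 1/√(1 − R²). The true type I error is 2·P(t₄₀ > 2.021 × that ratio).

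| R² (assumed) | SE ratio | True type I error |
|---|---|---|
| 0 | 1.00 | 5.0% |
| 0.09 | 1/√0.91 = 1.05 | 4.0% |
| 0.20 | 1/√0.80 = 1.12 | 2P(t₄₀ > 2.260) = 2.9% |
| 0.40 | 1/√0.60 = 1.29 | 2P(t₄₀ > 2.609) = 1.3% |

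Simulation with three strata agrees: about 3% and 1–2% in the last two rows.

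Simulation with two strata at r = 0.5 (R² = 0.25) shows where the error lies. The true standard error is 0.283 with or without ΔFS. The average reported value is 0.327 without ΔFS and 0.281 with it. Power at 0.9 SD, without and with ΔFS, is:
- 76% and 76% at r = 0
- 77% and 80% at r = 0.3
- 80% and 88% at r = 0.5

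With three strata and R² = 0.40 it is 81–82% and 93%.

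**Step 3: is a non-zero R² plausible?** The article's Treg figures allow a rough conversion, assuming half the patients are fast progressors and reading the 31% as fast against slow.
- If the gap is 31% of 2.1, it is 0.651. Then r = 0.651 × 0.5 / 0.7 = 0.465 and R² = 0.22.
- If it is 31% of the slow-progressor mean, that mean is 2.1 / 0.845 = 2.485 and the gap is 0.770. Then r = 0.55 and R² = 0.30.

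Both concern Treg level. The article gives nothing for change in Treg or for the other biomarkers.

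**Step 4: a prognostic covariate not used in stratification.** Power at 0.9 SD, 28 against 14, with imbalance judged at p < 0.05 (assumed):

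| r with outcome (assumed) | Adjust if unbalanced | Always adjust |
|---|---|---|
| 0.5 | about 78% | about 87% |
| 0.7 | about 78% | about 95% |

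At r = 0.1 the difference is about −0.3 points and at r = 0.2 about +0.9 points.

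For baseline as the covariate, with correlation ρ between baseline and follow-up, the variance of ANCOVA relative to a change score is (1 + ρ)/2: 0.65, 0.75 and 0.85 at ρ = 0.3, 0.5 and 0.7.

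**Step 5: choice after seeing the data.** With 4 to 8 independent candidate factors, the chance that at least one is flagged at p < 0.05 is 1 − 0.95⁴ = 19% to 1 − 0.95⁸ = 34%. A mechanical trigger keeps type I error at or below nominal. Only if an analyst took the smallest p-value over every subset of four covariates would it reach about 14%. That is a worst case, not something the article describes.

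**The case against.** The strongest reply is that the rule does little harm. It governs secondary outcomes in a study of biological activity, the ΔFS error is conservative, and a mechanical version does not inflate type I error. All of that stands.

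A reader might infer more than the article supports:

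- **That the primary result loses power.** It does not follow. The covariate sentence comes after the biomarker ANOVA, and the powered comparison of responder proportions is described separately. The linear-model figures above do not describe that test.
- **That false positives are inflated.** Omitting ΔFS lowers type I error, and the 14% figure needs a free search over models.
- **That omitting ΔFS throws away true precision.** In a linear model the estimate is about as precise either way; it is the reported standard error that is overstated. True precision comes from covariates not used in stratification, such as baseline.
- **That baseline is ignored or ΔFS forbidden.** Outcomes are changes from baseline, and the text does not exclude further terms. It states only one way of choosing them.

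It may also be said that covariate lists belong in the full protocol or SAP, or in the published methods cited for the biomarker models. That would answer mere silence. Here the article states the selection rule itself, twice, and a prespecified list elsewhere would have to replace it.

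**Conclusion.** The point holds for the secondary biomarker models and the survival analysis. As written, the rule would normally leave ΔFS out of the models and settles the remaining covariates after the data are seen.

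The consequence is over-wide intervals and lost power, not false positives. For ΔFS the size runs from nothing, if it is unrelated to the outcome, to a standard error about 1.1 or 1.3 times its true value if the strata explain 20% or 40% of variance. For a covariate outside the stratification, power rises from about 78% to 87% at r = 0.5 and hardly at all at r = 0.1.

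These figures rest on assumed correlations, an assumed 0.9 SD effect and linear models. No figure was calculated for the log-rank test or Cox model. The only link in the article between progression rate and a biomarker concerns Treg level, so the association with change may be weaker.

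**What to change.** Replace the imbalance trigger, in both places, with terms fixed in advance:

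- **Continuous outcomes:** arm, ΔFS stratum and the baseline value of the outcome.
- **Survival:** a log-rank test stratified by ΔFS, and a Cox model that includes ΔFS. Any further factor, such as age, should be named beforehand.
- **Imbalance-driven adjustment:** keep it, if wanted, only as a sensitivity analysis.

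The cost is a change of wording and one to three degrees of freedom. ΔFS is calculated at randomisation, and baseline measurements are already in the study flow chart (Table 3), so no new data or patients are needed.

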The secondary objectives include specific biological aims: (i) comparison between treated patients and control arm of Tregs'number and T cell subsets at different time points in blood and gut tissue samples; (ii) comparison between treated patients and control arm of neurophylaments and CSF cytokines and cells; (iii) analysis of fecal and saliva samples between the two groups to evaluate microbiota and cytokines' profile; (iv) FMT safety and tolerability in ALS; (v) clinical assessment (including tracheostomy-free survival, Forced vital capacity score, ALSFRS-R score, frequency of PEG or NIV); finally, (vi) the Quality of Life (QoL) assessment.

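### In the PEG/NIV/IV comparison, a patient who dies without a procedure is on the natural reading scored as procedure-free, which tilts this secondary odds ratio toward the arm with more early deaths

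*Protocol article*

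**What the plan says.** - **Outcome.** Outcome Measures lists "Frequency of procedures (PEG, NIV, IV) from baseline to month 3, 6, 9, 12" among the clinical outcomes compared between arms. Data Analysis repeats it: "Frequency of procedures (PEG, NIV, IV) will be compared from baseline to each time point in treatment vs. control arm". The secondary objectives at the end of the Introduction name only "frequency of PEG or NIV".
- **Model and success rule.** "The comparison of clinical endpoint among arms will be carried out by using the logistic regression model", with ORs and 95% confidence intervals. Then: "FMT will be considered effective in relation to controls whether the OR of positive results will provide a" p-value below 0.05. The test is two-sided.
- **Missing data.** One rule covers everything: "Last observation will be considered for patients with missing data". Neither death nor tracheotomy is excepted.
- **Starting status.** Table 1 excludes patients who have already had non-invasive ventilation, tracheotomy or gastrostomy.
- **Death.** It is scored only in a separate outcome, "Survival from onset and randomization to death or tracheotomy", compared by log-rank test with a Cox model for adjustment.

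The article does not say how a death before any procedure enters the procedure comparison. Nor does it say whether the three procedures are pooled, or what IV stands for.

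**The concern.** Death rules out a later procedure. Because all patients enter without one, the last recorded value of a patient who dies without a procedure is none. Carried forward, that value places the patient with those who never needed one, at every time point up to month 12. The worst outcome is then scored as the best.

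If deaths without a procedure are more frequent in one arm, that arm shows fewer procedures for this reason alone. An arm with excess mortality could look better on this outcome, and the article attaches an effectiveness statement to the OR. The trial is also meant to inform a later efficacy study, so an OR that can point the wrong way should not be carried into its design.

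A smaller textual matter sits beside this: the Introduction lists two components, while Outcome Measures and Data Analysis list three.

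**Working it through.** The article gives no expected procedure or death rate for this outcome, so there is no figure to reproduce. What follows is an illustration on assumed rates.

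**Inputs from the article:** 28 FMT and 14 control patients, 12 months, two-sided 0.05.

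**Assumed:** 12-month control rates of a first procedure (p = 30%) and of death without one (d = 5%, 10% or 15%); constant cause-specific hazards; on FMT the procedure hazard is unchanged and the death hazard doubled.

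**Formulas** (time unit 12 months, hazards λp and λd):
- From the control rates: λp + λd = −ln(1 − p − d), split in the ratio p : d.
- Proportion with a procedure, deaths counted as procedure-free: P = λp/(λp + λd) × [1 − exp(−(λp + λd))].
- Proportion with procedure or death: C = 1 − exp(−(λp + λd)).

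**Worked case, d = 10%:**
1. Control: λp + λd = −ln(0.60) = 0.5108, so λp = 0.3831 and λd = 0.1277.
2. FMT: λd = 0.2554, total 0.6385. C = 1 − exp(−0.6385) = 0.472. P = 0.6 × 0.472 = 0.283.
3. Procedure OR = (0.283/0.717)/(0.30/0.70) = 0.92.
4. Procedure-or-death OR = (0.472/0.528)/(0.40/0.60) = 1.34.

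| Control deaths without a procedure | Procedure OR | Procedure-or-death OR |
|---|---|---|
| 5% | 0.96 | 1.18 |
| 10% | 0.92 | 1.34 |
| 15% | 0.88 | 1.49 |

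With 40% procedures and 10% deaths the two ORs are 0.91 and 1.30. If the death hazards are equal, both ORs are 1.00 in every row.

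**Size in patients.** At d = 10% the FMT procedure rate falls from 30.0% to 28.3%, and 28 × (0.300 − 0.283) is about 0.47 of a patient.

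**Effect on the success rule.** By exact enumeration of two-sided Fisher tests at 28 against 14, the chance of a significant result favouring FMT rises from 1.6% with equal deaths to 2.1% at d = 10% and 2.4% at d = 15%.

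**If FMT works.** With both hazards halved, Fisher power is about 12.7% for procedures alone and 16.3% for procedure or death (d = 10%). Both are low.

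**The case against.** **The article is silent on death.** It does not call death missing data and does not define the denominator, and a condensed article may leave such handling to the full protocol or analysis plan. This stands in part: the scoring of death is a reading, not a statement. But the article does fix the model, the success rule and a missing-data rule without exception, and together these lead to the adverse scoring. The alternative, dropping deaths without a procedure from the denominator, removes the apparent benefit but still leaves those deaths unscored. In the worked case the odds become 0.283/0.528 = 0.536 against 0.30/0.60 = 0.50, an OR of 1.07, compared with 1.34 when deaths count.

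**Deaths are visible elsewhere.** Survival to death or tracheotomy is tested in its own right, and the safety board receives the relevant clinical data. This stands and limits the consequence, but it does not change the procedure OR.

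**The distortion is small.** This also stands: about half a patient in 28, hardly any change in the chance of a false claim, and nothing when deaths are balanced.

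**Stronger readings that the documents do not support.**
- A reader might infer that tracheotomised patients are also mis-scored. That could apply only if NIV is analysed on its own. If IV means invasive ventilation and the three procedures are pooled, a ventilated tracheotomised patient already counts as an event.
- A reader might object that tracheotomy enters both this outcome and survival. That is ordinary overlap between secondary outcomes.
- A reader might gauge the bias by how far an arm's rate moves once deaths are added. That compares two different endpoints: the rate moves even when deaths are equal and both ORs are 1.00.

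**Conclusion.** The point holds as a minor one. On the natural reading of the stated rules, death without a procedure is scored as procedure-free, and the procedure OR is biased toward the arm with more such deaths. Under the assumed rates (30% procedures, 5% to 15% deaths in controls, death hazard doubled on FMT) the procedure OR is 0.96 to 0.88 while the procedure-or-death OR is 1.18 to 1.49, so the sign reverses. This rests on assumed rates, constant hazards, a doubled death hazard and the last-observation rule being applied to deaths.

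It does not threaten the trial's main conclusion: the primary outcome is the Treg response, and this comparison is one of many secondary ones with low power under either scoring. The mismatch between the two-component and three-component lists is a plain inconsistency in the text.

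**What to change.** - In Outcome Measures and Data Analysis, define the outcome as the first of PEG, NIV, IV or death by each time point, so that a death before any procedure is an event.
- State that the last observation is not carried past death.
- As supporting description, report procedures and deaths without a procedure separately by arm, as cumulative incidence with death as the competing event. This display alone is not enough, because it shows the deaths but does not change the proportion with a procedure.
- Use one component list in the Introduction, Outcome Measures and Data Analysis, and spell out IV.

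The cost is wording only, since procedures and deaths are already recorded. There is a small downside: the composite includes deaths unrelated to nutrition or ventilation and partly overlaps the survival outcome.
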